**Study Design Diagram**

**
[figure not shown]
**

1. **Selection Criteria for Subjects**
   1. **Study Population**

cStage III gastric/gastroesophageal junction adenocarcinoma

- 1. **Inclusion Criteria**

1. Male or female patients aged 18–75 years with G/GEJ adenocarcinoma;
2. According to the AJCC 8th edition gastric cancer staging, patients with cStage III (cT_3-4a_N_1-3_M_0_) assessed by abdominal CT and G/GEJ adenocarcinoma diagnosed by gastroscopy and pathology (HER-2 negative or 1+); and patients with gastroesophageal junction (GEJ) cancer will only allow Siewert type III, and Siewert type II subjects who do not require combined thoracotomy to be enrolled.
3. Before enrollment, a doctor in charge of gastrointestinal surgery and an imaging technician jointly assess that the tumor is cStage III and qualified for the study of R0 resection with the purpose of cure, and the patient agrees to receive radical surgery and has no contraindication to surgery as judged by the surgeon;
4. No previous systemic therapy for the current disease, including surgical treatment, anti-tumor chemoradiotherapy/immunotherapy;
5. Expected survival of ≥3 months;
6. There are measurable tumor lesions according to RECIST v1.1 (see Attachment 3 for details);
7. ECOG PS score (see Attachment 4 for details) of 0–1 within 7 days after the first dose;
8. The heart is functioning well and resection for curative purposes can be performed. Patients with underlying ischaemic, valvular or other significant cardiac disease should be evaluated preoperatively by a cardiologist, if clinically indicated;
9. Primary organs are functioning normally and subjects are required to meet the following laboratory parameters:
   1. Absolute neutrophil count (ANC) ≥ 1.5 × 10^9^/L in the absence of granulocyte colony-stimulating factor in the past 14 days;
   2. Platelets ≥ 100 × 10^9^/L without transfusion in the past 14 days;
   3. Hemoglobin > 9 g/dL without or erythropoietin use within the past 14 days;
   4. Total bilirubin ≤ 1.5 × upper limit of normal (ULN); if total bilirubin > 1.5 × ULN but direct bilirubin ≤ ULN, the patient is also allowed to be enrolled;
   5. Aspartate aminotransferase (AST) and alanine aminotransferase (ALT) ≤ 2.5 × ULN
   6. Serum creatinine ≤ 1.5 × ULN and creatinine clearance (calculated using the Cockcroft-Gault formula) ≥ 60 ml/min;
   7. Good coagulation, defined as international normalized ratio (INR) or prothrombin time (PT) ≤ 1.5 times ULN;

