   8. Normal thyroid function, defined as thyroid stimulating hormone (TSH) within the normal range. If baseline TSH is outside the normal range, subjects with total T3 (or FT3) and FT4 within the normal range can also be enrolled;
   9. Myocardial enzymes within the normal range (subjects with isolated laboratory abnormalities judged as not clinically significant by the investigator are also allowed to be enrolled);
10. Thyroid function indicators: thyroid stimulating hormone (TSH) and free thyroxine (FT3/FT4) within the normal range or with mild and clinically insignificant abnormalities;
11. Body weight above 40 kg (including 40 kg), or BMI > 18.5;
12. Female patients must meet:

- Patients with menopausal (defined as no menses for at least 1 year and no other confirmed cause other than menopause) status, or who have been surgically sterilized (removal of ovaries and/or uterus), or who are of childbearing potential must also meet the following requirements:
- Pregnancy test must be negative within 7 days prior to first dose;
- Agree to use contraception with an annual failure rate of < 1% or remain abstinent (avoid heterosexual intercourse) from signing of informed consent through at least 120 days after the last dose of study drug and for at least 9 months after surgery (contraceptive methods with an annual failure rate of < 1% include bilateral tubal ligation, male sterilization, correct use of hormonal contraceptives that can inhibit ovulation, hormone-releasing intrauterine devices, and copper-containing intrauterine devices.) ;
- Do not breastfeed.

1. Male patients must meet:

Agree to practice abstinence (avoid heterosexual intercourse) or use contraception as defined below: Male patients must remain abstinent or use condoms correctly for at least 120 days after the last dose of study drug and for at least 9 months after surgery if the partner is a woman of childbearing potential or if the partner is pregnant. Reliability of sexual abstinence should be evaluated with reference to the duration of the clinical study, patient preferences, and lifestyle of daily living. Periodic abstinence (eg, calendar day, ovulation, basal body temperature, or post-ovulation contraceptive methods) and withdrawal are not acceptable methods of contraception;

1. Subjects read and fully understood the patient information and signed the informed consent form.
   1. **Exclusion Criteria**

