Imaging examinations will be performed to evaluate efficacy and feasibility of surgery after the completion of Cycles 2 and 3 of neoadjuvant therapy (within 7 days before the start of Cycle 3 and within 7 days after the end of Cycle 3). Imaging examinations are conducted after surgery and prior to adjuvant therapy, and pathological assessment will also be performed to evaluate the completeness of surgery. Evaluation requires a full abdominal direct contrast-enhanced (iodinated contrast) CT scan and gastric tumor MRI (contrast-enhanced). The same imaging technique should be used for pre- and post-evaluation in the same patient, and all imaging data must be retained. Patients who experience PD may continue the study treatment if they are willing and deemed suitable by the investigator to continue the original treatment regimen after re-signing the informed consent form, and re-evaluation will be performed after 4 weeks; otherwise, the patients will discontinue the study. For patients who discontinue treatment due to intolerable toxicity, if no efficacy evaluation is performed within 4 weeks prior to discontinuation, an efficacy evaluation should be conducted at the time of discontinuation.

For patients with potentially resectable gastric cancer after neoadjuvant therapy, surgery is scheduled within Weeks 2–6 after the completion of the last chemotherapy + immunotherapy. The surgical approach is determined based on the degree of disease response, including R0 resection, R1 resection, or cytoreductive surgery. The postoperative efficacy evaluation criteria primarily focus on surgical pathological assessment (complete pathological response rate, major pathological response rate, tumor regression grade, R0 resection rate, etc.), supplemented by imaging evaluation (objective response rate, disease control rate) for reference. At this point, the study has achieved its primary endpoint.

1. **Safety Reports and Adverse Event Management**
   1. **Definition of Adverse Event**

An adverse event (AE) is defined as any unfavorable and unintended medical occurrence in a clinical study participant from the time of signing the informed consent form, whether or not considered related to the study drug. AEs include, but are not limited to, the following circumstances:

- Exacerbation of pre-existing (prior to entering the clinical trial) medical conditions/diseases (including exacerbation of symptoms, signs, and abnormal laboratory findings);

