Per-protocol Set (PPS): Including all patients that comply with the study protocol, have good compliance, do not take prohibited medications during the study, and complete the required content in the case report forms. No imputation will be made for missing data. Statistical analyses of the drug's efficacy will be performed based on both the FAS and PPS.

Safety Analysis Set: Including all enrolled patients who have received at least one complete cycle of neoadjuvant immunotherapy plus chemotherapy and have safety records after using Serplulimab. This data set is used for safety analysis.

- 1. **Statistical Analysis Plan**

The results of this study will be primarily analyzed using statistical descriptive methods. For measurement data, the mean, standard deviation, median, max, and min values will be listed. For enumeration data and ranked data, the frequency (constituent ratio), rate, and CIs will be listed.

All statistical analyses will be programmed and calculated using SAS 9.2 Statistical Analysis Software. All statistical tests will be performed using two-sided tests, where P < 0.05 will be considered statistically significant for the tested differences, and CIs will be presented as 95% CIs.

- 1. **Efficacy Analysis**

The primary efficacy endpoint is the pCR rate. The ORR and its 95% CI will be calculated by the best overall response (BOR).

The Kaplan-Meier method will be used to plot the DFS curve and estimate the median DFS with its 95% CI, as well as the OS curve and its 95% CI.

Statistical analysis will be performed using SAS 9.4 software, where P < 0.05 will be considered statistically significant for the tested difference.

- 1. **Drug Safety Evaluation**

The AEs and adverse reactions that occurred in this study will be primarily described by descriptive statistical analysis, with a listing provided (adverse reactions are defined as “AEs with a ‘definitely related/probably related/possibly related’ relationship to the study drug”). The laboratory test results describe the conditions where values are normal before treatment but become abnormal afterward, along with the relationship with the study drug in case of abnormal changes. Chi-square test will be performed for the incidence of related adverse reactions between different stratified groups.

1. **Quality Control and Quality Assurance**

The study personnel must be physicians trained in clinical trials and work under the supervision of senior professionals.

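### The laboratory summary stated in Section 12.4 covers normal-to-abnormal changes, so worsening from a permitted abnormal baseline is left to investigator-judged adverse events

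*Protocol*

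**What the plan says.** Section 12.4 (Drug Safety Evaluation) first provides a descriptive summary and a listing of adverse events and adverse reactions. It then gives one rule for laboratory data: "The laboratory test results describe the conditions where values are normal before treatment but become abnormal afterward". The remainder of that sentence adds only causality. It names no category for a value that is already abnormal and gets worse, and no shift by grade.

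The inclusion criteria in Section 4 (item 9, repeated in the Synopsis) set these entry limits:

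- Liver enzymes: "Aspartate aminotransferase (AST) and alanine aminotransferase (ALT) ≤ 2.5 × ULN".
- Bilirubin: up to 1.5 × ULN, and "if total bilirubin > 1.5 × ULN but direct bilirubin ≤ ULN, the patient is also allowed to be enrolled".
- Creatinine: "Serum creatinine ≤ 1.5 × ULN and creatinine clearance" of at least 60 ml/min.
- Thyroid: "If baseline TSH is outside the normal range, subjects with total T3 (or FT3) and FT4 within the normal range can also be enrolled".
- Haemoglobin: "Hemoglobin > 9 g/dL without or erythropoietin use within the past 14 days".

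Section 11.1 counts worsening of a pre-existing condition as an adverse event, "including exacerbation of symptoms, signs, and abnormal laboratory findings". Section 11.4, under its heading on abnormal laboratory findings, asks for clinically significant abnormalities to be reported as adverse events and leaves that decision, for each abnormality, to the investigator.

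**The concern.** The laboratory rule and the entry limits do not fit together. The rule follows patients whose test was normal at entry. The entry limits admit patients whose test was not. For those patients and those tests, the stated summary has nothing to report, whatever the later course.

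Safety is part of the primary objective (Section 2.1), and the trial is open-label with a single arm. In that setting a laboratory summary is useful mainly because it rests on measured values and not on anyone's view of clinical significance. Here it provides no such check for the patients who begin closest to the higher toxicity grades, while it does describe trivial crossings of a normal limit.

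**Working it through.** The protocol gives no figure to reproduce, so the check sets the rule beside the entry limits and follows individual patients through both.

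**Step 1. Which tests may be abnormal at entry?**

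| Test | Permitted at entry | Abnormal baseline possible? |
|---|---|---|
| ALT/AST | ≤ 2.5 × ULN | Yes, above 1.0 and up to 2.5 × ULN |
| Creatinine | ≤ 1.5 × ULN, clearance ≥ 60 ml/min | Yes, above 1.0 and up to 1.5 × ULN, if the clearance condition is met |
| Total bilirubin | ≤ 1.5 × ULN, or higher if direct bilirubin ≤ ULN | Yes |
| TSH | Out of range if T3/FT3 and FT4 are normal | Yes |
| Haemoglobin | > 9 g/dL | Yes, if the lower limit of normal is above 9 g/dL (assumption; the protocol gives no limit) |

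**Step 2. Apply the Section 12.4 rule to example patients.**

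| Patient | Change | Normal before? | Described by the rule? |
|---|---|---|---|
| A | ALT 1.0 to 1.1 × ULN (a rise of 0.1/1.0 = 10%) | Yes | Yes |
| B | ALT 2.0 to 8.0 × ULN (8.0/2.0 = 4-fold) | No | No |
| C | ALT 2.5 to above 5 × ULN (more than 5/2.5 = 2-fold) | No | No |
| D | Haemoglobin 9.5 to 7.0 g/dL | No, under the assumption above | No |

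Patients B and C pass the level of 5 × ULN that the hepatitis row of the Section 8.2 table places in its Grade 3 or 4 category. That row goes by absolute level and takes no account of whether the baseline was normal. The laboratory summary therefore does not follow the severity scale used elsewhere in the protocol.

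**Step 3. Where else could B, C and D appear?** Section 11.1 makes worsening of an abnormal laboratory finding an adverse event. Section 11.3 has CTCAE grade changes of adverse events recorded. Section 12.4 summarises and lists adverse events. So they can appear there, subject to the investigator's judgment under Section 11.4. No other stated output counts them: the Section 12.2 descriptive statistics (mean, SD, median, maximum, minimum) do not pair a patient's baseline with that patient's worst value or count how many worsened.

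**Step 4. Size.** The number of patients with an abnormal baseline on each test is not given and cannot be derived. Planned enrolment is 30, and the Safety Analysis Set can be smaller because it requires one complete cycle and safety records. If the rate is taken over that whole set, each worsening patient left out lowers it by at least 1/30 = 3.3 percentage points. If the denominator is normal-baseline patients, the rate is not diluted but says nothing about the others. The protocol does not say which applies.

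**The case against.** The strongest case on the other side is that these patients are not lost to the trial. Section 2.2 defines the safety endpoint to include laboratory abnormalities, graded by CTCAE v5.0, and separately records Grade 3–4 adverse events from the start of neoadjuvant therapy to 30 days after surgery. The Synopsis adds treatment-related events of Grade 3 or higher. None of these needs a normal baseline. An ALT of 8 × ULN would be hard to judge clinically insignificant when the hepatitis row in Section 8.2 attaches a treatment action to that level. This stands, and it limits the point to the laboratory summary.

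Three stronger readings are tempting and are not supported:

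- A reader might infer that patients with an abnormal baseline can never be counted, however far they worsen. The adverse event route described above rules this out. Nor does Section 12.4 say that other laboratory descriptions are excluded; it simply names no other.
- A reader might infer a contradiction with Section 11.1. That section defines what an adverse event is; the laboratory sentence in Section 12.4 describes a different output, and the same section also analyses the adverse events. The two are not aligned, but they do not conflict.
- A reader might put a rate on the under-count. Suppose 20%, 40% or 60% of 30 patients are anaemic at entry, so that 6, 12 or 18 fall outside the rule, and 50% of all patients worsen. The line would then show 0.5 × 24/30 = 40%, 0.5 × 18/30 = 30% or 0.5 × 12/30 = 20%. The arithmetic is right, but the anaemia and worsening rates are assumed and the denominator of 30 is planned enrolment. These figures are not an estimate for this trial.

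It may also be said that shift tables belong in a statistical analysis plan. Their absence from a protocol would indeed be no error. The point here is that the protocol does fix a rule, and a plan that follows it inherits the gap.

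**Conclusion.** The point holds in a limited form. The one laboratory summary stated in Section 12.4 leaves out worsening from an abnormal baseline, which the entry criteria permit for ALT/AST, creatinine, bilirubin and TSH and, if the lower limit of normal is above 9 g/dL, for haemoglobin. As a patient-level finding, such worsening reaches the safety results only through adverse events that the investigator judges clinically significant. Severe changes are likely to be caught that way. Moderate worsening depends more on judgment, and the summary offers no independent check on it.

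This is a reporting weakness in the safety analysis. It does not touch the pCR analysis, and its size cannot be derived from the protocol. It is worth correcting because safety is part of the primary objective and the correction is cheap.

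**What to change.** In Section 12.4, replace the normal-to-abnormal rule with a shift table for each gradable test: baseline CTCAE v5.0 grade against worst on-study grade, for all patients in the safety analysis whatever their baseline. For tests without a CTCAE grade, such as TSH, use a low/normal/high shift. Report the number worsening by at least one grade and the number newly reaching Grade 3 or higher, and keep the relationship-to-drug description. State the denominator, the window for the worst value (the schedule includes a sample 3–7 days after surgery), and whether grades for a test abnormal at entry are set against the ULN or the patient's own baseline.

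The cost is one revised sentence and one table. Section 6.2 and the flow chart already schedule blood tests before the first dose, during neoadjuvant treatment, and before and after surgery, and CTCAE v5.0 is already the grading standard. No new data are needed and no clinical rule changes.
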